# *Zwakala Ndoda*: a cluster and individually randomized trial aimed at improving testing, linkage, and adherence to treatment for hard-to reach men in KwaZulu-Natal, South Africa

**DOI:** 10.1186/s13063-019-3908-0

**Published:** 2019-12-30

**Keywords:** Men, HIV testing, Linkages to care, KwaZulu-Natal, South Africa

## Abstract

**Background:**

Men in sub-Saharan Africa are less likely than women to get tested for HIV, less likely to present for treatment, less likely to be maintained in treatment, more likely to have detectable viral load, more likely to transmit HIV with unprotected intercourse, and more likely to progress to AIDS and die sooner from HIV. The ultimate objective of this research is to provide evidence-based strategies to improve HIV testing and treatment of HIV-infected men.

**Methods:**

This study is being conducted in the Greater Edendale Area and Vulindlela region in KwaZulu-Natal, South Africa. It is a two-stage design of a cluster-randomized trial and an individual randomized trial to test how structural and individual-level interventions address the demand-side factors that affect HIV testing and treatment for hard-to reach, high-risk men. It combines male-focused mobilization, community-based mobile HIV testing services, and a small incentive to determine if the strategies singly and in combination can result in more men diagnosed with HIV, and more men linked to and maintained in care with undetectable viral load.

**Discussion:**

A priority for sub-Sahara Africa is developing and evaluating novel and cost-effective strategies for identifying hard-to-reach groups such as men, linking them to HIV testing and care services, and maintaining them in care to the point of viral suppression. We propose a combination prevention intervention that addresses men’s individual, interpersonal, and structural barriers to testing and care. This includes male-led mobilization to encourage uptake of testing and treatment, male-focused testing venues, male-only counselors, developing counseling models that are flexible and responsive to men, and strategies for adhering to clinic visits without missing work and navigating the healthcare system. By thoughtfully combining male-focused mobilization, and testing and addressing some of the barriers to male engagement with health facilities, this study hopes to add to the growing evidence base about how to reach, test, link, and maintain a hard-to-reach group such as men in HIV treatment and care services.

**Trial registration:**

ClinicalTrials.gov, NCT03794245. Registered on 4 January 2019.

## Background

Men in sub-Saharan Africa are less likely than women to get tested for HIV, less likely to present for treatment, less likely to be maintained in treatment and have undetectable viral load (VL), and more likely to progress to AIDS and die sooner from HIV [1–5]. Currently, uptake of testing, linkage, and treatment falls below the levels required to decrease new infections in high-prevalence countries such as South Africa. All available analyses demonstrate that < 17% of HIV-positive individuals in South Africa know that they have HIV, are linked to care, and are maintained in care to reach VL suppression [6]. Doubling antiretroviral therapy (ART) coverage, even to 35%–40%, could reduce HIV infections by up to 40% [7]. The effects are even greater in high-prevalence areas such as KwaZulu-Natal (KZN) [7, 8]. Strategies for engaging the general population, and particularly hard-to-reach groups such as men [2, 4], through all steps of the treatment cascade are critical to epidemic control efforts in South Africa.

Several factors contribute to why men are a hard to reach population. HIV prevention and treatment programs have a blind spot regarding men [1, 2, 9, 10]. More than 30 years into the epidemic, interventions and research focusing on the prevention and care needs of men are notably absent [1, 2, 9–12]. Our attention thus far on women and girls is without dispute. Gender inequality is a key driver that impacts women’s health and access to HIV services and creates specific vulnerabilities for women to HIV infection [13, 14]. However, framing gender as women’s health means we have failed to understand how gender affects and drives the burden of ill health for men [9]. When men are included in HIV prevention and treatment, the focus is frequently on men as the problem (i.e. as transmitters of HIV), with outcomes that focus specifically on improving women’s health, not that of men [15, 16].

Male gender norms discourage men from engaging in testing and treatment [1, 11, 17, 18]. Unhealthy constructions of masculinity and male gender norms associated with toughness and control, sexual prowess, and heteronormativity as a way of asserting manhood can deter men from engaging with HIV services [2, 19–21]. Low testing and treatment engagement is fueled by perceptions of HIV as a threat to notions of masculinity, thus preventing men from testing early enough, disclosing their status, acknowledging their symptoms, or engaging with HIV treatment services [22, 23]. In Malawi, masculine ideals that require men to portray an aura of respectability, financial success, and as providers for their families are barriers to men engaging with testing and treatment services when they should [5, 24].

Key barriers to male engagement in HIV prevention and treatment include social and structural factors. HIV-related stigma and fear of disclosure leads to delays in HIV testing and treatment as well as poor adherence to medication among men [24–28]. Fear of ART side effects as well as misconceptions around the benefits of early diagnosis, care, and treatment can keep people who are living with HIV out of care [12, 29, 30]. Micro-structural factors such as poverty and employment migration keep men away from their partners and families for long periods of time [24]. This absence may make them more vulnerable to HIV infection due to sexual exposure and drug and alcohol use, and may delink them from local health services [3, 31, 32]. Further, health services are not considered male-friendly spaces, with operating hours that often clash with work obligations and provider attitudes that may lack sensitivity to men’s needs, further alienating them [29, 30, 33]. As a result, men have fewer opportunities and disproportionately poorer access to HIV prevention, care, and treatment services.

Existing evidence points to several strategies that could address male involvement in HIV prevention and treatment programs. Community mobilization has successfully changed gender inequitable norms through engaging men to question traditional masculinity and support each other to change social inequalities [34–39]. In our work in Project Accept NIMH/HPTN 043, uptake of HIV testing was improved by changing community norms through enhanced community participation, raising community awareness, and partnership building [40, 41]. Community mobilizing interventions have also demonstrated success in addressing stigma for marginalized populations, thus improving access to sexually transmitted illnesses (STI) care and treatment [42–44]. Programs that address male gender norms and masculinity constructions have a positive impact on men’s and women’s relationships, health, attitudes, and behavior [35, 45–48]. Effective community mobilization that addresses restrictive gender norms could motivate men to engage in testing, linkage to care, and treatment.

Community-based HIV testing services (HTS) optimize the treatment cascade by bringing testing closer to men (and women) thereby increasing demand. HTS, both mobile and home-based, have expanded the geographic coverage and reach of HTS (in both urban and rural locations) and addressed some of the convenience factors—time, costs, distance—typically associated with health facility HTS [49–54]. Our work and others have shown that community mobilization, coupled with mobile HTS targeted at venues frequented by men, can have a significant impact on increasing male engagement in treatment and prevention [11, 34, 49].

Economic incentives (EI) could address structural barriers to HIV testing for men [55]. A review assessing the effects of incentives on HIV/STI testing uptake demonstrated higher rates of uptake in the incentivized group in all seven studies [55]. In rural Malawi, Thornton examined a demand-side EI to randomize cash vouchers redeemable for the return of HIV test results and found that the incentive nearly doubled uptake of HIV testing [56, 57]. A study in Cape Town, South Africa found that greater proportions of the men who received an incentive (a food voucher of approximately US$10) were first-time testers (60.1% vs 42.0%) and had advanced disease (14.9% vs 7.5%) compared with men testing at the non-incentivized clinic services [58]. Finally, incentives in community-based settings [58–60] demonstrated more significant differences in uptake rates compared to incentives offered in clinical settings [61–63]. With demonstrated successes in other areas of health [64–68], including HIV, community-based incentives may encourage more men to take up testing [55, 58].

Once tested positive for HIV, individuals need to be effectively linked to care, treatment, and support services for early initiation of ART and sustained engagement in care. The drop-off that occurs at each step in the treatment cascade results in an estimated 2%–30% of those tested retained in care [69, 70]. There is a gendered slant to the treatment cascade: men are more likely to interrupt treatment [5], be lost to follow-up on ART [12, 16], present for treatment later and often start ART with more advanced HIV disease [5, 16], and experience additional complications than women [1]. Community-based testing and point-of-care (POC) diagnostics for HIV could address some of these challenges. The approach is able to effectively identify HIV-positive persons earlier in the course of their disease course and link people to care [71, 72]. A recent systematic review found that people using POC testing were more likely to both receive a CD4+ T-cell (CD4) result and start ART compared to those relying on laboratory-based methods [73]. In a South African study comparing two linkage-to-care strategies (mobile HTS referral letter versus laboratory CD4 count), the most commonly stated barrier to linkage was accessing public healthcare facilities during working hours and/or not getting time off work (41.4%) [71].

Community-based testing and treatment approaches that actively engage men and their communities, promotes men’s involvement, and is responsive to their needs are essential for developing effective responses to the epidemic in high-prevalence sub-Saharan Africa. This paper describes the protocol for the *Zwakala Ndoda* (an *isi*Zulu term inviting men to participate) study designed to respond to these needs in an area of extremely high HIV prevalence and incidence viz., KwaZulu-Natal, South Africa. Our study innovatively combines an evidence-based testing strategy (male-focused mobilization, community-based mobile HTS, and a small incentive) with proven, effective linkage-to-care strategies in one model. Our rigorous design allows us to test the individual and combined effects of novel strategies for HIV testing, linkage, and maintenance in care.

## Methods

### Study setting

This study is being conducted in the Greater Edendale Area (GEA) and Vulindlela region in KZN, South Africa. The area has a combined population of nearly 400,000 people spanning 20 municipal wards characterized by low population density, few infrastructure and developmental resources, high HIV prevalence (31%), high unemployment, and low per capita income (under US$2 per day) [25]. The population is primarily black African (99.3%). Nine of the wards fall under the tribal authority of a traditional leader or chief. Health services are provided through seven health facilities: Edendale Hospital, the main referral facility; two primary health clinics; and three satellite primary health clinics.

### Study aims

The study combines the best of three strategies (male-focused mobilization, community-based mobile HTS, and a small incentive) to determine if the strategies singly and in combination can result in more men diagnosed with HIV and more men linked to and maintained in care with undetectable VL. The specific aims are listed below.
Aim 1: To test the hypothesis, in a cluster-randomized design, that men-centered mobilization and testing strategies plus a small incentive will result in a substantially higher proportion of men getting tested for HIV (difference at least 30%).Aim 2: To test the hypothesis, in an individual randomized design, that POC CD4 testing combined with personalized linkage to care (PLC) will result in a higher proportion of HIV-positive men linked to and maintained in care with undetectable VL than POC alone and that both will be superior to standard of care.Aim 3: To integrate the outcomes of the structural and individual-level interventions and evaluate the joint effect of the structural and individual-level interventions on the percentage of HIV-positive men who are effectively treated (tested, linked to care, and maintained with undetectable VL).

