### Data analysis

#### Aim 1: Cluster-Randomized component

We will test the hypothesis that the community-wide proportion of men who were tested for HIV in the past year is at least by 10 percentage points (on an absolute scale) larger in communities randomized to the active intervention compared to the standard-of-care arm. The analysis will be based on testing reports provided by men included in the post-intervention assessment. Empirical proportions of tested participants will be calculated for each community and compared between the study arms by a two-sample Welch t-test. We will test the hypothesis that the difference in proportions is ≤ 0.1 against the alternative that the difference is > 0.1 at the one-sided level of 0.05.

#### Power calculations for Aim 1

We assumed 30% annual testing rates in the standard arm (similar to testing rates observed in Project ACCEPT in the community-based HTS arm in Vulindlela site) and between-community variance in testing rates 0.007 (estimated from Project ACCEPT’s Vulindlela data). Then, the sample size of four communities per arm, with 200 men sampled from each community, provides the following power for detecting intervention effects: power 0.05 for 10% difference (30% vs 40%, null hypothesis); power 0.36 for 20% difference (30% vs 50%); power 0.86 for 30% difference (30% vs 60%); and power 0.95 for 35% difference (30% vs 65%). Thus the study is powered to detect differences in testing rates that are substantially > 20% and therefore likely to be of practical significance. The power for detecting differences of ≥ 30% is large enough to be reasonably certain that such effects are not missed.

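### Aim 1 words its hypothesis as a difference of at least 30%, but the only planned test is against a 10-point margin, so significance alone would not show 30 points

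*Protocol article*

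**What the plan says.** The protocol article states the Aim 1 hypothesis in two places.

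- **Study aims.** Aim 1 is introduced as the test of a hypothesis: that the men-centered strategies plus incentive "will result in a substantially higher proportion of men getting tested for HIV (difference at least 30" per cent). The scale, absolute or relative, is not given.
- **Data analysis, Aim 1: Cluster-Randomized component.** The hypothesis is that the proportion tested "is at least by 10 percentage points (on an absolute scale) larger in communities randomized to the active intervention". The formal statement is "We will test the hypothesis that the difference in proportions is ≤ 0.1 against the alternative that the difference is > 0.1". The significance level is 0.05, one-sided. Community proportions are "compared between the study arms by a two-sample Welch t-test".

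The power paragraph labels the 10-point difference as the null hypothesis. It gives power of 0.05, 0.36, 0.86 and 0.95 at true differences of 10, 20, 30 and 35 points. The 30-point case is written as 30% versus 60%, which is an absolute difference.

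No passage relates the 30 in the aims to the 10 in the analysis, and no test against 30 points is planned.

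**The concern.** Both statements are presented as the hypothesis to be tested, on the same outcome, with different thresholds. What a significant Aim 1 result may be said to show depends on which one is meant. Rejecting the 10-point null supports a difference above 10 points. A reader who has only the aims could take the same result as confirming a difference of at least 30 points, which the test does not address. Conversely, an observed difference of, say, 25 points could be significant on the planned test and still fall short of the aim as worded.

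**Working it through.** **Inputs, all from the Aim 1 analysis and power paragraphs**

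- Control rate: "We assumed 30% annual testing rates in the standard arm".
- "between-community variance in testing rates 0.007".
- "the sample size of four communities per arm, with 200 men sampled from each community".
- Null difference 0.10, one-sided 0.05, Welch t-test on community proportions.

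**Step 1. Standard error of the difference.** The variance of one community's observed proportion is 0.007 + p(1 − p)/200.

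- Control, p = 0.30: 0.007 + 0.21/200 = 0.00805.
- Intervention, p = 0.60: 0.007 + 0.24/200 = 0.00820.
- SE = √((0.00805 + 0.00820)/4) = √0.0040625 = 0.0637.

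The SE barely moves with p; at p = 0.50 it is 0.0638.

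**Step 2. Reproduce the stated power against the 10-point margin.** Two methods were used: a noncentral t with 6 df and noncentrality (d − 0.10)/SE, and a simulation of the Welch test with Satterthwaite df, normal community effects, binomial sampling of 200 men and 400,000 runs.

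| True difference | Stated power | Noncentral t, 6 df | Welch simulation |
|---|---|---|---|
| 10 points | 0.05 | 0.05 | 0.044 |
| 20 points | 0.36 | 0.40 | 0.374 |
| 30 points | 0.86 | 0.87 | 0.845 |
| 35 points | 0.95 | 0.96 | 0.953 |

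The simulation agrees with all four stated figures to within 2 points. The noncentral t agrees except at 20 points. The result depends somewhat on the assumed shape of the community effects: beta effects give 0.836 at 30 points, and logit-normal effects, whose variance is set at the control rate and grows towards 50%, give 0.771. The stated figures nevertheless clearly belong to the 10-point test.

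**Step 3. What a significant result shows.** With t(0.95, 6 df) = 1.943, the half-width is 1.943 × 0.0637 = 0.124.

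- Smallest significant observed difference: 0.10 + 0.124 = 0.224, about 22 points.
- Observed difference of exactly 30 points: one-sided 95% lower bound 0.30 − 0.124 = 0.176, about 17.6 points.
- Observed difference needed for a lower bound above 30 points: 0.30 + 0.124 = 0.424, about 42 points.

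**Step 4. How often true differences below 30 points are significant.** By the noncentral t: 0.17 at 15 points, 0.40 at 20 (0.37 by simulation) and 0.67 at 25.

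**Step 5. Could 30 points have been the intended margin?** If the null were a difference of at most 30 points, this design would have power 0.05 at a true 30 points, 0.16 to 0.17 at 35 and 0.38 to 0.40 at 40. The plan proposes no such test. These figures show only that the design was not built around a 30-point margin.

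**The case against.** The strongest reply is that the analysis section leaves the analyst in no doubt. It alone gives a null, an alternative, a test and a level; it names 10 points as the null; and its power figures reproduce. The aim gives only a parenthesis, with no level or rule. The 30 matches the effect for which the power paragraph claims high power, and an expected effect in an aim is a common looseness. All of this stands. It places the fault in the wording of the aim and leaves the choice of analysis untouched.

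Three stronger readings are tempting, and the document does not support them.

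- *The trial has two competing decision rules.* It has one. Nothing says that an estimate below 30 points counts as failure, or that rejection will be reported as at least 30%.
- *A significant result can never support the aim.* Significance alone does not establish 30 points, but a large enough estimate would. Rejecting a 10-point margin also supports the looser claim of a substantially higher proportion, and is stricter than rejecting zero.
- *The 30% is relative.* Thirty per cent of the assumed 30% is 9 points, inside the planned null. But the analysis section specifies an absolute scale and writes its 30% difference as 30% versus 60%, so the absolute reading is the natural one. The aim merely fails to say so.

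What the reply does not remove is that the aim says the hypothesis being tested is a difference of at least 30%, and no such test is planned.

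**Conclusion.** The point holds as a misstated hypothesis in Aim 1. The planned test is of a 10-point margin, and 30 points is evidently the alternative at which power is 0.86, carried into the aim. A significant result establishes a difference above 10 points; by itself it does not establish one of at least 30.

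The gap is material. Significance needs an observed difference of about 22 points, whereas a lower bound above 30 needs about 42. Both figures assume that the observed SE is close to its expected 0.064, with about 6 df. With four communities per arm, the actual SE and the Satterthwaite df depend on the observed variances, so neither figure is a fixed cut-off.

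This should be fixed, because it governs what the primary Aim 1 result may be said to show. It does not call the design, the sample size, the test or the stated power into question, and the low power against a 30-point null is no defect of the trial, since that test is not planned.

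**What to change.** Reword Aim 1 so that it states the hypothesis actually tested: that the proportion of men tested is more than 10 percentage points higher, on the absolute scale, in intervention communities. Add that the trial has power 0.86 if the true difference is 30 points. In the report, do not present rejection of the 10-point null as confirmation of a 30-point difference.

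A useful optional addition is to report the estimated difference with a two-sided 90% interval. Its lower limit matches the one-sided 0.05 test and lets the reader see directly whether 30 points is supported.

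The cost is wording only. The stated aim becomes less ambitious; data collection, sample size and analysis are unchanged.

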#### Research design

This is a two-stage design of a cluster-randomized trial and an individual randomized trial to test how structural and individual-level interventions address the demand-side factors that affect HIV testing and treatment for hard-to-reach, high-risk men. A Standard Protocol Items: Recommendations for Interventional Trials (SPIRIT) diagram is presented in Fig. 1 and Additional file 1.

**Fig. 1 Fig1:**
[figure not shown]
Zwakala Ndoda Intervention SPIRIT *schematic*

#### Cluster-randomized study

Eight communities of approximately 5000 persons (four intervention and four control communities) from the GEA and Vulindlela regions will be selected with an equal mix of rural and peri-urban communities to ensure greater generalizability of the intervention in different settings. Each of the communities will be randomized to either men-centered mobilization and testing strategies plus a small incentive or the control condition. Randomization will be performed by the statistical center in a restricted way, so that four communities are assigned to each arm. Randomization code will be written in R and will use the Mersenne-Twister random number generator with seed derived from current system time.

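### Aim 1: communities are selected to mix rural and peri-urban settings, but setting is used neither in the stated randomization restriction nor in the Welch test, so about half of the possible draws (49%) leave the arms unbalanced on it

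*Protocol article*

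**What the plan says.** All references are to the Protocol article.

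- **Selection** (Cluster-randomized study): the communities "will be selected with an equal mix of rural and peri-urban communities to ensure greater generalizability of the intervention in different settings". The purpose given is generalizability.
- **Allocation** (same section): "Randomization will be performed by the statistical center in a restricted way, so that four communities are assigned to each arm". No stratification, pairing or constraint by setting is mentioned.
- **Analysis** (Aim 1: Cluster-Randomized component): "Empirical proportions of tested participants will be calculated for each community and compared between the study arms by a two-sample Welch t-test". The null hypothesis is that the "difference in proportions is ≤ 0.1 against the alternative that the difference is > 0.1 at the one-sided level of 0.05". No setting term appears.
- **Power** (Power calculations for Aim 1): "We assumed 30% annual testing rates in the standard arm", with "between-community variance in testing rates 0.007", four communities per arm and 200 men sampled in each. Stated power is 0.05, 0.36, 0.86 and 0.95 at true differences of 10, 20, 30 and 35 points. The variance is one overall figure, not divided by setting.

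**The concern.** Setting is the one community characteristic that the plan takes care to mix at selection, yet it plays no part in the stated allocation rule or in the test. With four communities per arm, an uneven split by setting is common. Access to testing may well differ between rural and peri-urban areas. If it does, an uneven split puts part of that difference into the arm comparison, where the null margin is only 10 points. For Aim 1 the article describes a post-intervention survey only, so it names no baseline testing rate that could be used to correct such a split.

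**Working it through.** **1. The plan's own power figures.** Inputs from Power calculations for Aim 1: control rate 0.30, between-community variance 0.007, 4 communities per arm, 200 men each, margin 0.10, one-sided 0.05. A simulated Welch test (normal community effects plus binomial sampling, 200,000 runs) gives:

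| True difference | Stated power | Simulated |
|---|---|---|
| 10 points | 0.05 | 0.045 |
| 20 points | 0.36 | 0.372 |
| 30 points | 0.86 | 0.844 |
| 35 points | 0.95 | 0.953 |

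The stated figures reproduce to within 2 points.

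**2. Chance of an uneven split.** Read the equal mix as 4 rural and 4 peri-urban. There are C(8,4) = 70 draws.

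- 2:2 in each arm: C(4,2) × C(4,2) = 36 (51.4%)
- 3:1: 2 × C(4,3) × C(4,1) = 32 (45.7%)
- 4:0: 2 (2.9%)
- Uneven: 34/70 = 48.6%

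**3. Shift in the arm difference.** Let D be the rural/peri-urban gap in testing rates. The article gives none, so D is an assumption, examined here at 0, 5 and 10 points. In a 3:1 split one arm's mean moves by +D/4 and the other's by −D/4, so the difference moves by D/2. In a 4:0 split it moves by D. At D = 0.10 a 3:1 split shifts the difference by 5 points.

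**4. Effect on the Welch test.** Total between-community variance is held at 0.007, so the variance within setting is 0.007 − D²/4 (0.0045 at D = 0.10). Simulated results:

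| D | Draw | Rejection at the 10-point null | Power at 30 points |
|---|---|---|---|
| 0 | average of all draws | 0.045 | 0.846 |
| 0.05 | 2:2 | 0.039 | 0.847 |
| 0.05 | 3:1, favourable / unfavourable | 0.083 / 0.017 | 0.919 / 0.759 |
| 0.05 | average of all draws | 0.045 | 0.842 |
| 0.10 | 2:2 | 0.021 | 0.856 |
| 0.10 | 3:1, favourable / unfavourable | 0.123 / 0.003 | 0.973 / 0.653 |
| 0.10 | average of all draws | 0.047 | 0.834 |

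**5. Allocation 2:2 within setting plus a setting term (5 df).** SE = √[(2v + 0.3×0.7/200 + 0.6×0.4/200)/4], with v the within-setting variance.

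- D = 0: √[(0.0140 + 0.00225)/4] = 0.064
- D = 0.10: √[(0.0090 + 0.00225)/4] = 0.053

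Simulated power at 30 points is 0.85, 0.87 and 0.94 for D = 0, 0.05 and 0.10, with type I error 0.05 throughout. Balancing the draw but keeping the unadjusted Welch test gains almost nothing: power 0.845 and 0.857 at D = 0.05 and 0.10, with type I error 0.039 and 0.020. Both parts are needed.

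**6. Adjustment after a draw already made.** In a 3:1 split arm and setting correlate at 0.5, so the variance of the adjusted arm effect is multiplied by 1/(1 − 0.25) = 4/3. At D = 0.10 the SE is 0.053 × √(4/3) = 0.061. Power at 30 points (noncentral t, 5 df, confirmed by simulation) is 0.75, 0.78 and 0.87 for D = 0, 0.05 and 0.10, and type I error is 0.05. In a 4:0 split arm and setting coincide, so the adjusted effect cannot be estimated.

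**The case against.** The design as described is valid. Drawing four of eight communities is proper randomization, a Welch test on cluster proportions is a proper cluster-level analysis, and the mix was chosen for generalizability, not for balance between arms. Before the draw there is no bias: variation due to setting is part of the between-community variance. All of this stands.

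A reader might infer that the trial runs a 12% type I error rate. The documents do not support that. The figure applies only to a 3:1 split in the favourable direction with an assumed 10-point gap; the mirror-image split gives 0.003, and the average over draws is 0.047 or less for the gaps shown.

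The gap is indeed an assumption. A 10-point gap would make setting account for 0.0025/0.007 = 36% of the between-community variance. The 0.007 comes from Vulindlela data of an earlier project, and the article does not say that it contains a rural/peri-urban component.

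A reader might also infer that adjusting for setting repairs any draw at small cost. It does not: after a 3:1 split with no gap, adjusted power is 0.75 against about 0.85 for Welch, and after a 4:0 split adjustment is impossible.

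Finally, this is a condensed article, and supportive adjusted analyses may be in the analysis plan. But it states the allocation rule and the Aim 1 test itself, and setting is in neither.

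**Conclusion.** The point holds as a design improvement, not as an error in the stated figures. As described, the plan has a 49% chance of an uneven split by setting and no stated adjustment for one. The consequence is conditional bias and lost precision: nothing if the settings do not differ, and with a 10-point gap a 5-point shift in a 3:1 split, with power at 30 points of 0.97 or about 0.65 according to direction. This rests on three assumptions: that equal mix means four and four, that the stated restriction is the only one, and that any gap lies within the 0.007 variance. If allocation was in fact balanced by setting, the imbalance falls away and only the missing setting term remains.

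**What to change.** **If the draw is still open:** randomize two of the four rural and two of the four peri-urban communities to each arm (36 admissible draws). Analyse community proportions with arm and setting (5 df) against the 10-point null. The cost is one line of randomization code and one degree of freedom. With no gap, simulated power at 30 points is still about 0.85.

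**If the draw has been made**, which is likely because Trial status dates the start of recruitment to August 2017: report the realised split, and fix the role of a setting-adjusted analysis before survey data are seen. Timing matters because, under Blinding, the statistician knows the assignments.

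- 2:2 split: arm plus setting as the primary analysis.
- 3:1 split: keep the Welch test and place the adjusted analysis beside it as a prespecified sensitivity analysis. It removes the setting bias, at the reduced power shown in step 6.
- 4:0 split: state that arm and setting cannot be separated.

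This costs a short addition to the analysis plan and no new data.
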